| PROMIS Sleep Disturbances                                                                                                                                                                                                                                                                                                                                                                                                                                                | 0.47(0.38,0.56)          | -5.58(-9.77,-1.39)   | -5.27(-9.12--1.41)                          | 0.63(0.51,0.76)          | -5.12(-8.27,-1.96) | -3.17(-6.47-0.14)                           |
| PROMIS Stress Experiences                                                                                                                                                                                                                                                                                                                                                                                                                                                | 0.69(0.61,0.77)          | -11.19(-17.11,-5.27) | -11.56(-17.78--5.35)                        | 0.61(0.49,0.72)          | -1.01(-7.1,5.09)          | -1.18(-6.48-4.12)                           |
| Estimates with 95% confidence intervals not covering zero are bolded.
† The range of the Dysfunctional Voiding Symptom Score (DVSS) is 0 to 30.
‡ The range of the Questionnaire for Urinary Issues – Kidney Stone Surgery (QUIKSS) is 0 to 56. QUIKSS is comprised of 16 items that used a frequency response scale and a 7-day recall period. Each item was scored from never (0) to always (4). The total score was the sum of the items. |                          |                             |                                             |                          |                           |                                             |

| eTable 10. Impact of Percutaneous Nephrolithotomy (PCNL) and Ureteroscopy (URS) on Patient-Reported Outcomes (PRO), by Age Group, at 1 Week Following Intervention |                                                                                                                                                                                                                                                                                                                                                                                                                                                                          |                              |                                         |                          |                     |                                         |                          |                              |                                         |                          |                            |                                         |
|--------------------------------------------------------------------------------------------------------------------------------------------------------------------|--------------------------------------------------------------------------------------------------------------------------------------------------------------------------------------------------------------------------------------------------------------------------------------------------------------------------------------------------------------------------------------------------------------------------------------------------------------------------|------------------------------|-----------------------------------------|--------------------------|---------------------|-----------------------------------------|--------------------------|------------------------------|-----------------------------------------|--------------------------|----------------------------|-----------------------------------------|
| Age                                                                                                                                                                | 8-11                                                                                                                                                                                                                                                                                                                                                                                                                                                                     |                              |                                         | 12-15                    |                     |                                         | 16-18                    |                              |                                         | 19-21                    |                            |                                         |
| PRO                                                                                                                                                                | Baseline (pre-op) effect                                                                                                                                                                                                                                                                                                                                                                                                                                                 | Procedure effect             | Difference in Difference for PCNL / URS | Baseline (pre-op) effect | Procedure effect    | Difference in Difference for PCNL / URS | Baseline (pre-op) effect | Procedure effect             | Difference in Difference for PCNL / URS | Baseline (pre-op) effect | Procedure effect           | Difference in Difference for PCNL / URS |
| DVSS † score (urinary symptoms)                                                                                                                         | 0.71 (0.49,0.93)                                                                                                                                                                                                                                                                                                                                                                                                                                                         | -0.63 (-2.9,1.65)            | 0.42 (-1.4-2.25)                        | 0.66 (0.52,0.81)         | 0.13 (- 2.52,2.77)  | 0.4 (-2.49-3.3)                         | 0.63 (0.51,0.76)         | 3.43 (- 1.42,8.28)           | 4.08 (-1.09-9.26)                       | 0.63 (0.39,0.87)         | 5.08 (3.23,6.92)    | 5.95 (4.37-7.54)                        |
| QUIKSS ‡ score (urinary symptoms)                                                                                                                       | 0.49 (0.24,0.75)                                                                                                                                                                                                                                                                                                                                                                                                                                                         | -7.89 (-15.75, -0.02) | -4.58 (-11.62-2.45)                     | 0.18 (0.02,0.34)         | -3.99 (- 12.08,4.1) | -2.82 (-16.15-10.52)                    | 0.4 (0.26,0.53)          | -4.71 (- 15.19,5.77)         | -1.05 (-14.26-12.15)                    | 0.11 (-0.22,0.44)        | -5.58 (-9.38,-1.77) | -1.98 (-7.62-3.67)                      |
| PROMIS Anxiety                                                                                                                                                     | 0.64 (0.49,0.8)                                                                                                                                                                                                                                                                                                                                                                                                                                                          | -9.24 (-16.09, -2.38) | -11.1 (-18.71--3.49)                    | 0.58 (0.47,0.69)         | -1.62 (- 5.95,2.71) | -3.38 (-8.14-1.37)                      | 0.59 (0.47,0.7)          | -7.62 (-13,-2.24)     | -3.89 (-11.74-3.97)                     | 0.64 (0.42,0.86)         | 7 (2.71,11.29)      | 12.49 (9.09-15.89)                      |
| PROMIS Pain Intensity                                                                                                                                              | 0.16 (- 0.02,0.34)                                                                                                                                                                                                                                                                                                                                                                                                                                                       | -7.94 (- 15.93,0.06)         | -3.49 (-14.37-7.39)                     | 0.23 (0.12,0.34)         | 1.51 (- 1.91,4.93)  | 0.12 (-4.93-5.16)                       | 0.23 (0.11,0.35)         | -9.6 (-17.45,-1.74)   | 0.03 (-9.22-9.27)                       | 0.45 (0.25,0.65)         | -1.03 (-3.05,0.98)         | -2.67 (-5.02--0.33)                     |
| PROMIS Pain Interference                                                                                                                                           | 0.16 (0,0.33)                                                                                                                                                                                                                                                                                                                                                                                                                                                            | -6.91 (- 18.12,4.3)          | -4.23 (-21.31-12.86)                    | 0.25 (0.14,0.36)         | -0.7 (- 3.65,2.24)  | -3.19 (-8.58-2.19)                      | 0.21 (0.09,0.33)         | -11.14 (-20.09,-2.19)        | 3.01 (-8.56-14.58)                      | 0.29 (0.06,0.51)         | 0.34 (-5.56,6.24)          | 7.99 (-9.91-25.88)                      |
| PROMIS Peer Relationships                                                                                                                                          | 0.61 (0.45,0.77)                                                                                                                                                                                                                                                                                                                                                                                                                                                         | 0.87 (- 3.79,5.52)           | 0.11 (-5.08-5.29)                       | 0.69 (0.58,0.8)          | 1.86 (- 3.12,6.84)  | 3.63 (-1.33-8.58)                       | 0.7 (0.59,0.8)           | 2.33 (- 5.68,10.35)          | 2.86 (-5.62-11.34)                      | 0.55 (0.24,0.86)         | -3.76 (-8.72,1.2)          | 2.03 (0.18-3.87)                        |
| PROMIS Sleep Disturbances                                                                                                                                          | 0.66 (0.46,0.86)                                                                                                                                                                                                                                                                                                                                                                                                                                                         | -4.06 (- 9.59,1.47)          | -3.75 (-8.75-1.25)                      | 0.5 (0.37,0.64)          | -2.38 (-5.9,1.13)   | -3.86 (-5.98--1.73)                     | 0.45 (0.34,0.57)         | -9.55 (-14.62,-4.47)  | -6.21 (-12.85-0.43)                     | 0.55 (0.31,0.78)         | 0.35 (-2.22,2.92)          | -1.66 (-4.42-1.11)                      |
| PROMIS Stress Experiences                                                                                                                                          | 0.63 (0.45,0.81)                                                                                                                                                                                                                                                                                                                                                                                                                                                         | -12.61 (-19.34,-5.89)        | -13.53 (-21.02--6.04)                   | 0.65 (0.54,0.75)         | 0.27 (- 3.93,4.47)  | -1.8 (-5.67-2.07)                       | 0.62 (0.5,0.74)          | -10.87 (-21.18,-0.56) | -9.94 (-22.53-2.66)                     | 0.8 (0.6,0.99)           | 4.87 (-1.25, 10.99) | 8.55 (4.04-13.06)                       |
|                                                                                                                                                                    | Estimates with 95% confidence intervals not covering zero are bolded.
† The range of the Dysfunctional Voiding Symptom Score (DVSS) is 0 to 30.
‡ The range of the Questionnaire for Urinary Issues – Kidney Stone Surgery (QUIKSS) is 0 to 56. QUIKSS is comprised of 16 items that used a frequency response scale and a 7-day recall period. Each item was scored from never (0) to always (4). The total score was the sum of the items. |                              |                                         |                          |                     |                                         |                          |                              |                                         |                          |                            |                                         |

| Table 11. Stone Clearance for Percutaneous Nephrolithotomy (PCNL) and Ureteroscopy (URS)
Considering Ultrasonographic Images Obtained From 0 to 16 Weeks After Surgery, Overall and by Stone
Size and Stone Location |                             |                     |                       |
|-----------------------------------------------------------------------------------------------------------------------------------------------------------------------------------------------------------------------------------|-----------------------------|---------------------|-----------------------|
|                                                                                                                                                                                                                                   | Weighted PCNL vs URS |                     |                       |
|                                                                                                                                                                                                                                   | PCNL                 | URS          | PCNL-URS       |
| Stone Clearance, %
(95% CI)                                                                                                                                                                                            | 72.4
(55.2-89.7)         | 72.1
(68.9-75.4) | 0.3
(-17.2-17.8)   |
| Stone size                                                                                                                                                                                                                 |                             |                     |                       |
| <7 mm                                                                                                                                                                                                                             | 53.2
(0.0-100.0)         | 78.6
(74.3- 83)  | -25.4
(-80.7-29.9) |
| 7-10 mm                                                                                                                                                                                                                           | 46.5
(0.0-100.0)         | 65
(58.5-71.6)   | -18.5
(-88-50.9)   |
| 10-15 mm                                                                                                                                                                                                                          | 75.5
(49.7- 100.0)       | 61
(50.4-71.6)   | 14.5
(-13.4-42.4)  |
| >15 mm                                                                                                                                                                                                                            | 92.5
(81.6-100.0)        | 57.1
(40.6-73.7) | 35.3
(15.5-55.1)   |
| Stone location                                                                                                                                                                                                             |                             |                     |                       |
| Lower pole kidney                                                                                                                                                                                                                 | 44.2
(3.3-85)            | 65.7
(57.8-73.6) | -21.5
(-63.1-20.1) |
| Non-lower pole kidney                                                                                                                                                                                                             | 77.3
(54.9- 99.6)        | 57.8
(51.1-64.6) | 19.4
(-3.9-42.8)   |
| Ureter                                                                                                                                                                                                                            | 83.4
(54.1- 100.0)       | 81.1
(77-100.0)  | 2.2
(-27.3-31.8)   |

**eTable 12.** Stone Clearance for Percutaneous Nephrolithotomy (PCNL) and Ureteroscopy (URS) Considering Sensitivity and Specificity of Ultrasonographic Images on Centralized Imaging Review, Overall and by Stone Size and Stone Location

|                                        | Weighted PCNL vs URS |                     |                       |
|----------------------------------------|-----------------------------|---------------------|-----------------------|
|                                        | PCNL                 | URS          | PCNL-URS       |
| Stone Clearance, %
(95% CI) | 63.9
(41.8-86.1)         | 70.5
(66.2-74.7) | -6.5
(-29.1-16.1)  |
| Stone size                      |                             |                     |                       |
| <7 mm                                  | 48.9
(0.0-100.0)         | 78.1
(72.2-83.9) | -29.2
(-85.2-26.8) |
| 7-10 mm                                | 42.9
(0.0-100.0)         | 64.1
(55.7-72.5) | -21.2
(-89.9-47.5) |
| 10-15 mm                               | 65.5
(29.6-100.0)        | 59.3
(45.5-73.1) | 6.2
(-32.2-44.6)   |
| >15 mm                                 | 93.1
(81-100.0)          | 51.4
(29.1-73.7) | 41.7
(16.3-67.1)   |
| Stone location                  |                             |                     |                       |
| Lower pole kidney                      | 44
(0.7-87.3)            | 60.7
(50.5-70.9) | -16.7
(-61.2-27.8) |
| Non-lower pole kidney                  | 68.1
(38.4-97.9)         | 55
(45.9-64.2)   | 13.1
(-18-44.2)    |
| Ureter                                 | 72.5
(28-100.0)          | 81.2
(75.8-86.6) | -8.7
(-53.5-36.1)  |

| eTable 13. Stone Clearance for Percutaneous Nephrolithotomy (PCNL) and Ureteroscopy (URS)
Based on Multiple Imputation for Missing Ultrasonographic Data at the 4- to 8-Week Interval,
Overall and by Stone Size and Stone Location |                             |                     |                       |
|--------------------------------------------------------------------------------------------------------------------------------------------------------------------------------------------------------------------------------------------------|-----------------------------|---------------------|-----------------------|
|                                                                                                                                                                                                                                                  | Weighted PCNL vs URS |                     |                       |
|                                                                                                                                                                                                                                                  | PCNL                 | URS          | PCNL-URS       |
| Stone Clearance, %
(95% CI)                                                                                                                                                                                                           | 66.7
(50.5-82.9)         | 73.1
(70.4-75.7) | -6.4
(-22.8-10)    |
| Stone size                                                                                                                                                                                                                                |                             |                     |                       |
| <7 mm                                                                                                                                                                                                                                            | 61.0
(16.4-100.0)        | 80.1
(75.1-85.1) | -19.1
(-63.6-25.4) |
| 7-10 mm                                                                                                                                                                                                                                          | 41.9
(0.0-90.6)          | 66.9
(61.2-72.7) | -25.0
(-73.7-23.8) |
| 10-15 mm                                                                                                                                                                                                                                         | 65.2
(30.4-100.0)        | 57.7
(44.2-71.3) | 7.5
(-27.6-42.5)   |
| >15 mm                                                                                                                                                                                                                                           | 81.1
(44.2-100.0)        | 60.3
(45.5-75.2) | 20.7
(-15.4-56.8)  |
| Stone location                                                                                                                                                                                                                            |                             |                     |                       |
| Lower pole kidney                                                                                                                                                                                                                                | 51.9
(13.3-90.5)         | 63.8
(54.2-73.3) | -11.9
(-52.9-29.1) |
| Non-lower pole kidney                                                                                                                                                                                                                            | 62.6
(24.5-100.0)        | 59.2
(52.7-65.7) | 3.4
(-35.5-42.2)   |
| Ureter                                                                                                                                                                                                                                           | 74.6
(39.9-100.0)        | 84.2
(80.6-87.9) | -9.7
(-43.9-24.6)  |

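### eTable 10, ages 19-21: the intervals for pain intensity, peer relationships and sleep are about 40% to 60% of the width that at most 15 PCNL and 83 URS patients would give

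*Combined protocol and SAP*

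**What the plan says.** eTable 10 reports, for each patient-reported outcome (PRO) and age group at 1 week, a baseline slope, a procedure effect and a difference in difference (DiD) between PCNL and URS. For ages 19-21 the DiD column gives:

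- anxiety: "12.49 (9.09-15.89"
- pain intensity, after a minus sign: "2.67 (-5.02--0.33"
- peer relationships: "2.03 (0.18-3.87"
- sleep, after a minus sign: "1.66 (-4.42-1.11"
- pain interference: "7.99 (-9.91-25.88"

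The footnote says "Estimates with 95% confidence intervals not covering zero are bolded".

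eTable 4 counts 15 PCNL and 83 URS patients aged 19-21 in the enrolled cohort. Protocol 3.3.1 admits participants who complete no questionnaires, so 15 is an upper limit on PCNL responders.

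The SAP (Outcome model) specifies inverse-probability-weighted regression, with PROs adjusted for baseline. It names no variance estimator, weight truncation, effective sample size or small-sample correction. The SAP (Missing data) applies 20 imputations with Rubin's rules to the week-1 PROs and to the heterogeneity analyses. Protocol 6.4 calls the heterogeneity analyses descriptive and intended for later synthesis.

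**The concern.** The age group with the fewest PCNL patients has the narrowest DiD interval in 5 of the 8 PROs. Weighting and imputation normally widen intervals, yet several of these are narrower than a simple unweighted comparison of 15 with 83 patients would give.

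Calling a subgroup analysis descriptive excuses low power. It does not excuse wrong error bars. If the results are meant for synthesis, an SE that is half its proper size gives that cell about four times its proper inverse-variance weight. A clinician counselling a young adult would also take the subgroup differences as better established than they are.

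**Working it through.** **Inputs.** Group sizes of 15 and 83 are from eTable 4, baseline SDs (all ages, weighted) from eTable 8, and baseline slopes b and intervals for ages 19-21 from eTable 10. For anxiety the slope is "0.64 (0.42,0.86".

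**Printed SE** = (upper − lower)/3.92. Pain intensity: 4.69/3.92 = 1.20. Peer: 3.69/3.92 = 0.94. Sleep: 5.53/3.92 = 1.41.

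**Expected SE** = s × √(1/15 + 1/83) = s × 0.2806. Two choices of s are used, with b standing in for the pre/post correlation: the baseline-adjusted residual SD, SD√(1 − b²), and the change-score SD, SD√(2(1 − b)).

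| DiD, ages 19-21 | SD | b | s (adjusted; change) | Expected SE | Printed SE | Printed/expected |
|---|---|---|---|---|---|---|
| Pain intensity | 9.61 | 0.45 | 8.58; 10.08 | 2.41-2.83 | 1.20 | 0.42-0.50 |
| Peer relationships | 8.47 | 0.55 | 7.07; 8.04 | 1.98-2.25 | 0.94 | 0.42-0.47 |
| Sleep | 10.20 | 0.55 | 8.52; 9.68 | 2.39-2.71 | 1.41 | 0.52-0.59 |
| Anxiety | 10.91 | 0.64 | 8.38; 9.26 | 2.35-2.60 | 1.73 | 0.67-0.74 |
| QUIKSS | 11.49 | 0.11 | 11.42; 15.33 | 3.20-4.30 | 2.88 | 0.67-0.90 |
| DVSS | 4.38 | 0.63 | 3.40; 3.77 | 0.95-1.06 | 0.81 | 0.76-0.85 |
| Stress | 9.92 | 0.80 | 5.95; 6.27 | 1.67-1.76 | 2.30 | 1.31-1.38 |
| Pain interference | 11.80 | 0.29 | 11.29; 14.06 | 3.17-3.95 | 9.13 | 2.31-2.88 |

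**Could a high correlation explain it?** Setting the change-score SE equal to the printed SE and solving for the correlation gives 0.90 (pain intensity), 0.92 (peer) and 0.88 (sleep). The upper limits of the printed slopes are 0.65, 0.86 and 0.78. Anxiety needs 0.84, which lies inside its slope interval.

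**How many PCNL patients would the printed SEs need?** Treating the URS mean as known, which favours the table, n = s²/SE²: about 51-71 (pain intensity), 56-73 (peer) and 36-47 (sleep). With URS held at 83, pain intensity and peer need about 135-177 by the adjusted formula and 490-600 by the change-score formula.

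**Peer in detail.** The 83 URS patients alone contribute 7.07/√83 = 0.78 to 8.04/√83 = 0.88 of the printed 0.94. To leave room for 15 PCNL patients, their SD would have to be about 1.3-2.1 points, against 7.1-8.0 expected.

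**Effect on conclusions** (half-width = 1.96 × expected SE):

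- Pain intensity: −2.67 ± 4.72 is −7.39 to 2.05, and ± 5.54 is −8.21 to 2.87. Both cover zero.
- Peer: 2.03 ± 3.89 is −1.86 to 5.92, and ± 4.42 is −2.39 to 6.45. Both cover zero.
- Sleep already covers zero.
- Anxiety: 12.49 ± 5.09 is 7.40 to 17.58, which still excludes zero.

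**Procedure-effect column** (expected SE by the adjusted formula):

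- Clearly narrow: pain intensity 4.03/3.92 = 1.03 against 2.41; sleep 5.14/3.92 = 1.31 against 2.39; QUIKSS 7.61/3.92 = 1.94 against 3.20.
- About as expected: anxiety 2.19 against 2.35; pain interference 3.01 against 3.17; DVSS 0.94 against 0.95.
- Wider: peer 2.53 against 1.98; stress 3.12 against 1.67.

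The QUIKSS effect is bolded. At the expected width, −5.58 ± 6.28 is −11.86 to 0.70, which covers zero.

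**Across age groups.** For 24, 32, 22 and 15 PCNL patients (youngest to oldest), the DiD half-widths are 10.88, 5.04, 9.25 and 2.34 for pain intensity, and 5.19, 4.96, 8.48 and 1.84 for peer.

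**The case against.** Neither the SD nor the number of responders at ages 19-21 is published. The check borrows an all-ages baseline SD, assumes a similar spread at week 1, and uses a regression slope as a correlation. A quieter subgroup would have narrower intervals: anxiety is attainable if its SD is about two-thirds of the overall one. This stands for anxiety, and the DVSS and QUIKSS DiD intervals are only modestly narrow. For pain intensity and peer the subgroup SD would have to be half the overall one or less. The stress and pain interference intervals from the same age group point the other way.

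The SAP's baseline-adjusted model corresponds most closely to the procedure effect, and in that column peer and anxiety show no marked shortfall. This also stands, so the peer finding concerns the DiD column only. Still, an SE that goes from 2.53 to 0.94 between columns for peer, and from 3.01 to 9.13 for pain interference, needs explaining.

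Three stronger readings are tempting, and the documents do not support them:

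- **That the variance method produces the anxiety reversal** between ages 8-11 (−11.1) and 19-21 (12.49). A variance estimator does not move point estimates. The widened interval, 7.40 to 17.58, still lies above that for ages 8-11 (−18.71 to −3.49).
- **That the table flags these DiD cells as excluding zero.** In the age 19-21 columns, bold appears only on procedure effects.
- **That variance collapse is established.** No estimator is named. A table error is possible: the bolded stress procedure effect for ages 19-21 has limits of −1.25 and 10.99, against the table's own footnote.

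**Conclusion.** The concern holds for three DiD intervals at ages 19-21. Pain intensity, peer relationships and sleep are printed at 42-59% of the width expected from at most 15 and 83 unweighted patients. It also holds for the procedure effects for pain intensity, sleep and QUIKSS, at 43%, 55% and 61%. Three results that now exclude zero would cover it: the pain intensity and peer DiDs and the bolded QUIKSS procedure effect.

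This rests on a subgroup SD close to the overall baseline SD and on the slope as an approximate correlation. Using the enrolled count of 15 and ignoring weighting both favour the table.

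Intervals that are too narrow and too wide within one small subgroup are what an unstable large-sample variance on a very small effective sample would produce. That remains an inference. The primary outcome is not affected, and no calculation was made for the sex subgroups in eTable 9.

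**What to change.** 1. Check the eTable 10 entries for ages 19-21 against the analysis output, including which estimates are bolded.
2. Name the variance estimator in the SAP. Re-run the age-subgroup PRO intervals either with a small-sample corrected variance (for example CR2 or HC3 with t degrees of freedom) or with a patient-level bootstrap that re-estimates the propensity weights in each resample. Combine either one with the multiple imputation.
3. Report the number of PCNL responders and the effective sample size for each cell, so that readers can see how many patients carry each estimate.
4. Apply the same method to eTable 9 for consistency.

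The cost is a short SAP addition and a modest re-analysis of existing data. The bootstrap is the heavier option because it must be combined with 20 imputations. Many intervals will be wider, and some subgroup results will no longer exclude zero.
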